| 22:00                                                | 06:00 | Sleep study                                                 |
| 06:00                                                | 08:00 | venous blood sampling, clinical examination, questionnaires |
| 08:00                                                | 08:45 | Breakfast                                                   |
| 08:45                                                | 09:30 | Driving simulator                                           |
| 09:30                                                | 10:15 | Psychomotor vigilance test                                  |
| 10:15                                                | 11:00 | Snowboard-simulator                                         |
| 11:00                                                | 11:45 | Motor Task Manager                                          |
| 11:45                                                | 12:30 | Pulse wave analysis                                         |
| 12:30                                                | 13:30 | Lunch                                                       |
| 13:30                                                | 14:00 | Spirometry&DLCO                                             |
| 14:00                                                | 17:00 | Leisure time (transfer to next location if applicable)      |

The time table represents one example of a sequence of evaluations. During the assessment periods in the evenings and mornings subjects will rotate through different sequences of tests each lasting for 45 min. The order of tests will vary according to availability of measurement techniques.

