##### 9.1.2.2 Pulmonary function testing

In order to detect subclinical High Altitude Pulmonary Edema Spirometry including diffusion capacity will be performed according to standard techniquesA3, A4. In cases of subclinical HAPE vital capacity as well as the diffusion capacity will be reduced due to increased intrapulmonary fluid accumulation.

A3) ATS/ERS task force. Standardization of spirometry. Eur Respir J 2005;26:319-338.

A4) ATS/ERS task force. Standardization of the single breath uptake of carbon monoxide in the lung. Eur Respir J 2005;26:720-735. A2) O. Senn et al.. Med Sci.Sports Exerc. 38 (9):1565-1570, 2006.

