#### **9.1.4.1 Augmentation index (AIx) measured by pulse wave analysis**

Pulse wave analysis is a technique which uses applanation tonometry to assess the arterial pressure waveform. The pressure within an artery is a composite of both the forward ejected wave and the reflected waves travelling back to the heart. In healthy arteries, the reflected waves travel slowly and reach the heart in diastole thereby enhancing coronary perfusion. If the vasculature is stiffened, the reflected waves travel faster and reach the heart in systole, thus

augmenting systolic pressure. Systemic arterial stiffness can be measured using augmentation index (AIx), calculated as the difference between the second systolic peak and inflection point, expressed as a percentage of the central pulse pressure. AIx decreases in response to vasodilators (e.g. nitro-glycerine, salbutamol) by reduction of smooth muscle tone, and it has been demonstrated that AIx falls following inhaled salbutamol as a result of endothelial dependent nitric oxide release. Therefore, an impaired decrease of AIx after inhalation of salbutamol is a display of endothelial dysfunction. Pulse wave analysis is performed with a micro manometer (SphygmoCor, At-Cor Medical) which records radial artery pulse waveforms continuously. Mean values of approximately 10 pulse waves are used for analyses. A validated transfer function is used to generate a corresponding central aortic pressure waveform as described previously and AIx is then calculated. After a baseline recording, salbutamol is administered by inhalation (400 µg), and a re-evaluation of the pulse wave is performed after 10 minutes. Endothelial independent vasodilatation is assessed by pulse wave analysis as described above 3 minutes after sublingual application of nitro-glycerine 0.5 mg.

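### Spirometry/DLCO is timetabled after a session that gives salbutamol and nitroglycerin, and each subject's test order is not held constant across locations, so lung function and the morning PVT carry avoidable variation

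*Protocol*

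**What the plan says.** Table 3 (section 7.1.1, phase 1) lists the morning tests in 45-minute slots from 08:45: driving simulator, PVT (09:30-10:15), snowboard simulator, Motor Task Manager and, in the slot from 11:45, "12:30 | Pulse wave analysis". After lunch, the slot from 13:30 reads "14:00 | Spirometry&DLCO". Tables 5 and 6 (sections 7.2.1 and 7.2.2, phase 2) print the same order for normal and restricted sleep.

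The pulse wave session is also a drug challenge. Section 9.1.4.1 says "After a baseline recording, salbutamol is administered by inhalation (400 µg), and a re-evaluation of the pulse wave is performed after 10 minutes", and a further reading is taken "3 minutes after sublingual application of nitro-glycerine 0.5 mg".

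The purpose of the lung function tests is given in section 9.1.2.2: "In order to detect subclinical High Altitude Pulmonary Edema Spirometry including diffusion capacity will be performed according to standard techniques". The same section expects vital capacity and diffusion capacity to fall if there is edema.

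The note under Table 3 says "The time table represents one example of a sequence of evaluations", has subjects rotate through the 45-minute tests in the evening and morning, and ends: "The order of tests will vary according to availability of measurement techniques". Tables 5 and 6 carry no such note.

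Sections 7.1 and 7.2 say that the evaluations are identical across locations. They do not say that order or clock time is. No interval is set between the drugs and any later test.

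**The concern.** Two features of the timetable meet here.

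First, a test meant to pick up small losses of lung function comes after a bronchodilator and a vasodilator in every printed timetable. Its slot is 30 minutes long and lies after lunch, so it appears to sit outside the 45-minute morning rotation. While it stays there it follows the drugs wherever the pulse wave session falls, but at a varying interval.

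Second, the PVT and the pulse wave session both occupy 45-minute morning slots, and equipment availability decides which comes first. The cross-over randomises the sequence of altitudes; it does not control test order within a day. The comparison of interest is within subject, between altitudes, so a change in a subject's order from one location to the next enters that comparison directly. If it is haphazard it is noise. If it follows the site it is bias, because site and altitude are the same thing in this design.

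Pulmonary function is a primary objective (section 6.1) and PVT reaction time is a primary outcome (section 7.3.1).

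**Working it through.** The protocol gives no figure for this point that could be reproduced. The check is clock arithmetic, followed by a sensitivity calculation whose assumptions are marked.

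**1. Printed interval from drugs to spirometry (Tables 3, 5, 6).**
- End of pulse wave session to start of spirometry: 13:30 − 12:30 = 60 min.
- Start of pulse wave session to start of spirometry: 13:30 − 11:45 = 105 min.
- Assume that both drugs are given within the slot, nitroglycerin after the salbutamol reading (the order of description in section 9.1.4.1). Salbutamol is then given no later than 12:30 − 10 − 3 min = 12:17, that is 73-105 min before spirometry. Nitroglycerin is given between 11:55 and 12:27, that is 63-95 min before.

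**2. Interval under rotation, spirometry kept at 13:30.** The five morning slots end at 09:30, 10:15, 11:00, 11:45 and 12:30. The gap from the end of the pulse wave session to spirometry is then 240, 195, 150, 105 or 60 min.

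**3. PVT under rotation.** In the printed example the morning PVT precedes the drugs. Over all 120 orders of the five morning tests, it follows the pulse wave session in 60 (50%). Over the five cyclic rotations of the printed order, it follows in 3. Its start can move between 08:45 and 11:45, a span of 3 hours. These shares describe what free rotation permits; actual order depends on equipment.

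**4. Possible bias in the PVT altitude contrast.**
Bias = shift in reaction time when tested after the drugs × difference between altitudes in the share tested after the drugs. Neither factor is in the documents, so both are assumptions. The relevant difference of 25 ms is from section 12.

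| Assumed shift | Share difference 0 | Share difference 0.5 |
|---|---|---|
| 2 ms | 0 | 1 ms (4% of 25) |
| 5 ms | 0 | 2.5 ms (10%) |
| 10 ms | 0 | 5 ms (20%) |

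**5. Possible noise when order is haphazard.** If each session independently has probability 0.5 of following the drugs, a shift d adds d² × (0.25 + 0.25) = d²/2 to the variance of the difference between two sessions. For d = 2, 5 and 10 ms this is 2, 12.5 and 50 ms². Section 12 gives an SD of 30 ms. Taking that as the SD of the within-subject difference (an assumption; the section does not say), the variance is 900 ms², and the added noise is 0.2%, 1.4% or 5.6% of it.

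**6. Lung function.** The documents give neither the size nor the duration of either drug's effect on vital capacity or diffusion capacity, so only the interval can be computed.

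**The case against.** A reader might infer that lung function and the PVT are measured under a drug effect that differs between altitudes. The documents do not support that.

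- The printed gap between drugs and spirometry is the same at every location, so a constant effect largely cancels in a within-subject contrast.
- The printed morning PVT comes before the drugs, there is also an evening PVT, and section 7.3.1 does not say which session supplies the primary outcome.
- Nothing says that equipment availability differs by site.
- Spirometry and diffusion capacity are additional outcomes in section 7.3.2, not primary ones.
- Section 12 plans multiple regression, so recorded order or clock time could be a covariate.

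Most of this stands, and it limits the point. Three things remain. Cancellation requires the drug response itself to be the same at each altitude, whereas section 5.3.1 hypothesises endothelial dysfunction at altitude, which section 9.1.4.1 assesses by an altered salbutamol response. That concerns vessels, and the protocol makes no such claim for the lung, so it is a reason for caution and not evidence of bias. Adjustment for order works only if order is recorded and does not follow site. And the statement that evaluations are identical cannot be read as fixing order, because the Table 3 note expressly lets order vary.

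**Conclusion.** The point holds as a matter of avoidable variation. In all three printed timetables lung function follows the drug session by about 60-105 min, and the phase 1 note lets a subject's morning PVT fall on either side of the drugs, at different clock times, at different altitudes. Whether the rotation also applies in phase 2 is not stated.

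The sure consequence is a loss of standardisation. Bias in the altitude contrast is only a possibility: it needs order to differ systematically by site, or the drugs' effect on the measured variable to differ by altitude. For the PVT, the 1-5 ms range (4-20% of the relevant difference) rests on assumed shifts and an assumed 0.5 difference in shares, and is 0 if shares are equal; the 20% end should not be read as an estimate. For lung function no size can be given. Severity is low to moderate; the case for changing the plan is that the remedy is cheap.

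**What to change.** Amend the note to Table 3, and Tables 5 and 6, to say that each subject keeps the same test order and the same clock times at every location and under both sleep conditions. Different subjects may have different orders among the tests that precede the drugs. Schedule the PVT, the simulators, the Motor Task Manager and spirometry/DLCO before the pulse wave session, for example by moving spirometry/DLCO ahead of it. The drug challenge itself stays as described in section 9.1.4.1. Record the actual start time of each test so that departures can be seen.

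This need not lengthen the day. Pulse wave session, lunch and spirometry take 45 + 60 + 30 = 135 min, which is the span from 11:45 to 14:00 in whatever order they are placed.

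The cost is less scheduling flexibility and possible queueing at the pulse wave station, since every subject would reach it late in the sequence. The pulse wave session would also move relative to lunch or the clock, but equally at every location. If queueing rules this out, holding each subject's order and times constant across locations still removes the order difference from the altitude contrast, although lung function would then remain a measurement made after the drugs and should be reported as such.

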## 7.2 DETAILED STUDY DESIGN FOR THE STUDY PHASE 2 EVALUATING THE COMBINED EFFECTS OF SLEEP RESTRICTION AND ALTITUDE

The purpose is to investigate the combined effects of hypobaric hypoxia at altitude and sleep restriction on sleep, breathing, psychomotor performance and cardiovascular function. A randomized, 2x2 balanced cross-over design will be used to control for the factors altitude and sleep restriction, respectively. The study will comprise 2 periods of 4 days, i.e. a total of 8 days. Within each study period, 2 days will be spent in Zurich and 2 days at altitude (Davos Jakobshorn, 2590m). The two periods will be separated by a 7 days wash-out period. In the week before study entry and during the wash-out period, subjects will maintain mandatory bed times in darkness from 22:00 to 06:00 h verified by actimetry. During the 4 h sleep restriction, sleep will be scheduled between 02:00 to 06:00h.

Subjects will be informed to refrain from driving during and on the day after the phase of sleep restriction.

During non-restriction trials subjects will have mandatory bed times in darkness between 22:00 to 06:00h. After recruitment, individuals will be randomized to one of 4 different sequences of studies as shown in table 4 and figure 3. Evaluations at all locations will be identical.

| Table 4. Sequences of evaluation in study phase 2           |                                                          |                                                          |                                                          |
|-------------------------------------------------------------|----------------------------------------------------------|----------------------------------------------------------|----------------------------------------------------------|
| Day -60 to 0: Subject screening, recruitment, randomization |                                                          |                                                          |                                                          |
| Sequence A                                                  | Sequence B                                               | Sequence C                                               | Sequence D                                               |
| Restricted sleep
490m, 2 days
2590m, 2 days    | Restricted sleep
2590m, 2 days
490m, 2 days | Normal Sleep
490m, 2 days
2590m, 2 days     | Normal Sleep
2590m, 2 days
490m, 2 days     |
| 7 d wash-out                                                | 7 d wash-out                                             | 7 d wash-out                                             | 7 d wash-out                                             |
| Normal Sleep
490m, 2 days
2590m, 2 days        | Normal Sleep
2590m, 2 days
490m, 2 days     | Restricted sleep
490m, 2 days
2590m, 2 days | Restricted sleep
2590m, 2 days
490m, 2 days |

[figure not shown]

Figure 3: Study phase 2 design representing subject flow and the 4 different sequences of evaluations. Study locations comprise the Clinical Trial Center, University Hospital of Zurich (Zurich, 490m) and the Hotel at Jakobshorn, Davos (Davos J, 2590m). At both locations single room sleep laboratories and a control room for supervising researchers will be installed.

Randomization: This is performed in a similar way as for study phase 1 (see above)

### 7.2.1 Schedule of daily assessments study phase 2, normal sleep

During normal sleep periods subjects will have mandatory bed-times in darkness between 22:00 to 06:00h. Bed-times and darkness will be verified by the supervising researchers.

| Table 5. Daily evaluations study phase 2, normal sleep |       |                                                             |
|---------------------------------------------------------------|-------|-------------------------------------------------------------|
| from                                                          | to    | Activity                                                    |
|                                                               | 17:00 | arrival, transfer to rooms                                  |
| 17:15                                                         | 18:00 | Clinical examination, questionnaires                        |
| 18:00                                                         | 19:00 | Dinner                                                      |
| 19:00                                                         | 19:45 | Driving simulator                                           |
| 19:45                                                         | 20:30 | Psychomotor vigilance test                                  |
| 20:30                                                         | 21:15 | Snowboard-simulator                                         |
| 21:15                                                         | 22:00 | Motor Task Manager                                          |
| 22:00                                                         | 06:00 | Sleep study                                                 |
| 06:00                                                         | 08:00 | venous blood sampling, clinical examination, questionnaires |
| 08:00                                                         | 08:45 | Breakfast                                                   |
| 08:45                                                         | 09:30 | Driving simulator                                           |
| 09:30                                                         | 10:15 | Psychomotor vigilance test                                  |
| 10:15                                                         | 11:00 | Snowboard-simulator                                         |
| 11:00                                                         | 11:45 | Motor Task Manager                                          |
| 11:45                                                         | 12:30 | Pulse wave analysis                                         |
| 12:30                                                         | 13:30 | Lunch                                                       |
| 13:30                                                         | 14:00 | Spirometry&DLCO                                             |
| 14:00                                                         | 17:00 | Leisure time (transfer to next location if applicable)      |

### 7.2.2 Schedule of daily assessments study phase 2, restricted sleep

Restricted sleep means supervised sleep duration of 4 h per night between 02:00 to 06:00h with mandatory bed-times in darkness between 2:00 to 06:00h. Sleep restriction will be ensured by supervised entertainment (e.g. board/card games, watching TV) until bed-time at 02:00.

| Table 6. Daily evaluations study phase 2, restricted sleep |       |                                                             |
|-------------------------------------------------------------------|-------|-------------------------------------------------------------|
| from                                                              | to    | activity                                                    |
|                                                                   | 17:00 | arrival, transfer to rooms                                  |
| 17:15                                                             | 18:00 | Clinical examination, questionnaires                        |
| 18:00                                                             | 19:00 | dinner                                                      |
| 19:00                                                             | 19:45 | Driving simulator                                           |
| 19:45                                                             | 20:30 | Psychomotor vigilance test                                  |
| 20:30                                                             | 21:15 | Snowboard-simulator                                         |
| 21:15                                                             | 22:00 | Motor Task Manager                                          |
| 22:00                                                             | 02:00 | Evening program to keep subjects awake (see above)          |
| 02:00                                                             | 06:00 | Sleep study                                                 |
| 06:00                                                             | 08:00 | venous blood sampling, clinical examination, questionnaires |
| 08:00                                                             | 08:45 | Breakfast                                                   |
| 08:45                                                             | 09:30 | Driving simulator                                           |
| 09:30                                                             | 10:15 | Psychomotor vigilance test                                  |
| 10:15                                                             | 11:00 | Snowboard-simulator                                         |
| 11:00                                                             | 11:45 | Motor Task Manager                                          |
| 11:45                                                             | 12:30 | Pulse wave analysis                                         |
| 12:30                                                             | 13:30 | lunch                                                       |
| 13:30                                                             | 14:00 | Spirometry&DLCO                                             |
| 14:00                                                             | 17:00 | Leisure time (transfer to next location if applicable)      |

## 7.3 STUDY OUTCOME MEASURES

### 7.3.1 Primary outcomes

- Sleep disordered breathing (number of apneas/hypopneas)
- Sleep quality (sleep efficiency, amount of slow wave sleep)
- Vigilance (Psychomotor vigilance test reaction time)
- Cardiovascular function (mean nocturnal heart rate)

### 7.3.2 Additional outcomes

- Breathing patterns, ventilation and gas exchange assessed by noninvasive means (oxygen saturation, transcutaneous and end-tidal carbon dioxide tension, respiratory inductive plethysmography to measure minute ventilation and spirometry as well as carbon monoxide diffusion )

- Quantitative sleep analysis assessed by EEG power spectral analysis and by slow wave morphometry
- Subjective sleep quality by visual analog scale
- Psychomotor performance and vigilance assessed by the Motor Task Manager, a computer based test of complex motor skills; driving simulator and snow board simulator performance
- ECG derived heart rate, arrhythmia, heart rate variability measures of autonomic function; blood pressure, indices of arterial stiffness and endothelial function assessed by sphygmomanometry and noninvasive applanation tonometry of the radial artery
- Blood markers of systemic inflammation (CRP, IL-6, TNF-alpha, TGF-beta), cardiovascular function (BNP, cell-derived micro particles) and insulin sensitivity.

